## Abstract

**Background:**

Mild traumatic brain injury (mTBI) is a common pediatric condition with growing recognition of its impact on mental health. While most children recover within weeks of the injury, a subset experience persistent emotional symptoms, including anxiety and depression. Early identification of youth at risk for adverse mental health outcomes is essential for timely intervention. Our primary study objective is to develop a robust clinical prediction tool to identify children at risk for adverse mental health outcomes after mTBI.

**Methods:**

We will conduct a multicenter prospective observational cohort study enrolling patients aged 11–17 years who present to the emergency department (ED) with mTBI within 3 days from injury. We will enroll consecutive patients into separate derivation and validation cohorts using different enrolling sites. Baseline data, including pre-injury mental health status, and clinical variables will be collected from patients, caregivers, and ED clinicians. We will collect validated measures during the acute period (1 to 2 weeks), 1-month, and 3-months post-injury including: the Generalized Anxiety Disorder-7 (GAD-7), Patient Health Questionnaire-8 (PHQ-8), Pediatric Quality of Life Inventory (PedsQL), Rivermead Post-Concussion Symptoms Questionnaire, and the Strengths and Difficulties Questionnaire (SDQ). Our primary outcome is a composite measure of clinically significant new or worsening in anxiety or depression at 1 or 3 months. Secondary outcomes include persistent post-concussive symptoms, reduced quality of life, and new behavioral or emotional difficulties. We will analyze associations between baseline factors and outcomes to derive and validate a clinical prediction tool.

**Discussion:**

Our study will provide a comprehensive assessment of mental health and other outcomes following mTBI in adolescents and identify predisposing factors for adverse outcomes. Our findings will contribute to the development of a clinical prediction tool to support early identification and referral for at-risk youth. Study results may inform post-injury care pathways and targeted interventions aimed at improving long-term recovery.

**Trial registration:**

ClinicalTrials.gov Identifier: NCT06370520. Registered March 20, 2024. The study protocol has been approved by the Institutional Review Boards at all participating sites.

**Supplementary Information:**

The online version contains supplementary material available at 10.1186/s12887-026-06788-5.

## Background

Mental health sequelae are common in adolescents after mild traumatic brain injuries (mTBI). As defined by the Centers for Disease Control and Prevention (CDC), mTBI includes concussion, an acute brain injury resulting in neurological symptoms. These injuries are associated with a Glasgow Coma Scale (GCS) score of 13 to 15 in association with confusion or disorientation, loss of consciousness, amnesia, seizures, or other signs or symptoms of head injury [1, 2]. mTBI in children is a major public health concern in the United States (US) and globally and is associated with decreased health-related quality of life following injury [3–5]. After youth mTBI, cognitive and functional activity tends to return to baseline within three months [6]. However, neuropsychiatric recovery is more complex. In prior studies, 25–50% of children with mTBI had substantial mental health sequelae after head injury, with depression and anxiety the most common [7–10]. Anxiety and depression may be a result of injury or may develop or worsen due to lingering symptoms or restrictions after injury [11]. 

Identification of adolescents at risk for mental health sequelae after mTBI is a key knowledge gap. The CDC Guidelines on the Diagnosis and Management of mTBI among Children, published in 2018, recommend that health care professionals screen for known risk factors for persistent symptoms in children with mTBI [2]. Prior studies have identified risk factors for mental health sequelae after mTBI [12–21]. These factors include socioeconomic status, severity of injury, and pre-existing and family history of psychiatric disorders. Unfortunately, most of these studies include small cohorts (*n* < 200) and are thus unable to provide sufficient evidence for a robust and precise prediction tool that clinicians can use to risk stratify children after mTBI.

Because no single factor is strongly predictive of mental health sequelae, identifying children at risk is challenging. One validated clinical prediction tool identifies children with mTBI at risk for persistent concussive symptoms at 28-days; [22] however, there are no clinical prediction tools that specifically address risk factors for mental health sequelae [2]. As such, prior studies have demonstrated that 31–78% of children with mTBI who have new or worsening mental health concerns are not receiving appropriate mental health care [23–25]. The primary objective of our study is to develop a robust clinical prediction tool to identify children at risk for adverse mental health outcomes after mTBI. This tool will fill an important gap in the field and assist health care providers in managing adolescents with mTBI.

## Methods

### Study design and setting

We will conduct a multicenter, prospective observational study of adolescents with mTBI to develop a clinical prediction tool that identifies those at risk for adverse mental health outcomes. The study will be conducted in six emergency departments (EDs) across the United States. All sites are American College of Surgeons (ACS) verified Level I pediatric trauma centers.

Participants will be enrolled into two sequential cohorts: a derivation cohort at four sites and a validation cohort at three sites. The clinical coordinating center will enroll in both the derivation and validation cohorts to monitor enrollment throughout the study. This design constitutes a true external validation, as the prediction tool will be derived and tested on an independent patient population than the derivation cohort. External validation is considered a more rigorous approach than internal validation, which uses the same cohort for both derivation and testing.

The clinical prediction tool will first be derived using only the derivation cohort. Investigators will remain blinded to the data from the validation cohort until the prediction tool has been fully developed. The finalized tool will then be validated in the second, independent cohort.

This study will follow the STROBE (Strengthening the Reporting of Observational Studies in Epidemiology) guidelines, and a completed checklist will be included with manuscript submission (see Additional File 1) [26]. 

### Participants

We will enroll adolescents aged 11 to 17 years who present to the ED within 72 h of mTBI. We will use the CDC definition of mTBI, which is an acute brain injury resulting in neurological symptoms such as confusion or disorientation, headache, nausea, loss of consciousness, amnesia, seizure, focal neurological signs or symptoms, and/or traumatic intracranial abnormalities on computed tomography (CT) or magnetic resonance imaging (MRI), in association with Glasgow Coma Scale (GCS) scores of 13 to 15. Consistent with CDC precedent, this definition includes commonly used terms such as “concussion” or “minor head injury” [13]. Participants may include patients with neuroimaging findings indicative of traumatic abnormalities (e.g., intracranial hemorrhage, diffuse axonal injury, skull fractures), as these are considered risk factors for later mental health sequelae [9, 11, 27]. However, neuroimaging is not required for study enrollment.

Patients will be excluded if any of the following apply:

Presentation to the ED more than 72 h after injury.TBI requiring emergent neurosurgical intervention at enrollment.Other injuries requiring emergent surgery at enrollment.Inability of the patient or parent to accurately complete study questionnaires due to preexisting functional limitations (e.g., severe intellectual development).Previous known enrollment into the study.Inability of the patient or parent to speak English or Spanish.

### Participant screening and consent

Injured children aged 11 to 17 years presenting to the ED will be screened by either research coordinators or treating clinicians. For all patients who meet the inclusion criteria, we will complete an eligibility case report form to document inclusion and exclusion criteria. These data will inform the STROBE-compliant flowchart [26]. To ensure that the study sample is representative of the broader mTBI population, electronic health records for injured children aged 11 to 17 years seen in the ED will be routinely reviewed throughout the enrollment period. If a potentially eligible patient is not approached for enrollment, the research coordinator will complete a brief form capturing basic demographic and clinical information available retrospectively. This process will support assessment of potential enrollment bias.

Eligible patients will be approached by a research coordinator or treating clinician. We will obtain verbal informed consent from a parent or caregiver. Parents or caregivers will receive a one-page information sheet outlining the study purpose, procedures, risks and benefits, compensation, and contact details for research staff and the institutional review board. Information sheets will be available in both English and Spanish. If a parent or caregiver declines participation, the reason for non-participation will be recorded on the eligibility case report form, and the patient will not be enrolled. Upon enrollment, parents or caregivers will electronically provide their contact information for questionnaire completion.

### Validated questionnaires

We have selected validated questionnaires based on availability in English and Spanish languages, feasibility of completion, and recommendations by the CDC, which include the NIH TBI common data elements [28]. 

Generalized Anxiety Disorder-7 (GAD-7): The GAD-7 questionnaire is a widely used self-report measure to screen for anxiety symptoms and severity. It consists of seven questions related to anxiety with responses scored from 0 (no symptoms) to 3 (symptoms nearly every day). It has been validated as a diagnostic tool for generalized anxiety disorder in adults and adolescents, panic disorder, social phobia, and post-traumatic stress disorder (70–90% sensitivity and 80–90% specificity across disorders) [29–32]. The GAD-7 has been used as an anxiety measure for prior mTBI studies in adolescents [33]. A cutoff of 10 points or higher (maximum is 21 points) is frequently used to determine a higher risk for disability and functional impairment. A change of 4 points on the GAD-7 is the minimal clinically important difference [34]. Higher GAD-7 scores correlate with worse disability and functionality. The questionnaire is available in English and Spanish and takes two minutes to complete.

Patient Health Questionnaire-8 (PHQ-8): The PHQ-8 is the self-report major depressive disorder module of the full PHQ and is used to diagnose depression and grade severity of symptoms in both medical and mental health settings [35]. It consists of 8 questions related to depression and responses are scored from 0 (“no symptoms”) to 3 (“symptoms nearly every day”). It is similar to the PHQ-9, which has been validated in adults and adolescents [36, 37], and has been used to assess depression in prior mTBI studies in adolescents [33, 38], but does not include a question about potential suicidality (“How often have you had thoughts that you would be better off dead, or thoughts of hurting yourself in some way”) [37, 39]. The PHQ-8 is used frequently in place of the PHQ-9 in large studies because it is often infeasible to provide appropriate psychiatric intervention should the potential suicidality question be answered positively [40]. The PHQ-8 has similar discriminatory capacity as the PHQ-9 [40]. A cutoff of 10 points or more (out of 24) would correlate to a moderate or higher severity of depression symptoms and has excellent sensitivity and specificity in various populations [41–43]. The minimal clinically important difference is a change of 5 points on the PHQ-8 [44]. Higher PHQ-8 scores are associated with decreased functional status and increased symptom-related difficulties, sick days, and healthcare use [42]. The PHQ-8 is available in English and Spanish and takes less than two minutes to complete. 

The Rivermead Post-Concussion Symptoms Questionnaire (Rivermead): This self-report questionnaire is a frequently used and validated measure to evaluate for symptoms after mTBI and is a NIH core common data element for symptoms [45–47]. Symptoms are rated from 0 to 4, where 0 = no symptoms at all; 1 = no more of a problem than before injury; 2 = a mild problem compared to before injury; 3 = a moderate problem compared to before injury; and 4 = a severe problem compared to before injury. The Rivermead is available in English and Spanish and takes about five minutes to complete.

Pediatric Quality of Life Inventory (PedsQL): The PedsQL has been reported in more than 850 publications and measures health-related quality of life in healthy children and adolescents as well as those with acute and chronic health conditions [48]. There are age-appropriate versions for the PedsQL, including 8–12 years and 13–18 years in the adolescent age range, and age-appropriate versions can be combined for analysis. The PedsQL Generic Core scales are comprised of 23 questions that measure core dimensions of health as delineated by the WHO. The four multidimensional scales include: physical (8 items), emotional (5 items), social (5 items), and school functioning (5 items). The PedsQL is developmentally appropriate, reliable, and valid (distinguishes between healthy children and children with acute and chronic health conditions). For TBI, the PedsQL reliably differentiates between TBI severity in children [49]. The PedsQL is measured as a continuous score that ranges from 0 to 100, and a clinically meaningful difference is indicated by a 4.5-point change on the PedsQL scale [50]. The PedsQL is recommended by the NINDS Common Data Elements TBI Outcomes Workgroup as a core quality-of-life measure post-TBI and a primary measure of global outcome [51]. It is available in English and Spanish and takes approximately five minutes to complete. We will be collecting both self and proxy PedsQL reports.

Strengths and Difficulties Questionnaire (SDQ): We will use the SDQ standardized caregiver-report questionnaire to measure emotional symptoms, conduct problems, inattention/hyperactivity, and peer relationship problems. The 20 questions that make up these 4 scales are used to calculate a composite “total difficulties” score [52]. Each of the items are rated as “not true”, “somewhat true”, and “certainly true”. For this study, we will use the emotional distress and hyperactivity/inattention sub-scales (5-items each) to assess for parent-reported psychological distress and hyperactivity/inattention of the patient. We will use a cutoff score of 5 or more points to define psychological distress and 6 or more points to define hyperactivity/inattention [52]. These cutoff scores have a population base rate of less than 10%. The SDQ is a core common data element for psychological status in TBI. The SDQ is available in English and Spanish and takes less than five minutes to complete.

Early Physical Activity/Return to School Questionnaire: Early physical activity is defined as any level of physical activity, other than no activity, seven days after the index ED visit [12]. Return to physical activity within seven days of injury is associated with lower rates of post-concussive symptoms [12, 18]. We will assess for this early physical activity using a single self-report question categorized as no activity (e.g., physical rest), light to moderate aerobic activity (e.g., walking, swimming, stationary cycling, or jogging); heavy aerobic activity (e.g., running) or non-contact training drills (e.g., passing drills with teammates); and full-contact practice or games (e.g., normal training and return to competition).

Similarly, early return to school (defined as < 3 school days missed) is associated with lower post-concussive symptom burden at 14 days [53]. We will assess early return to school using a single self-report question 1 to 2 weeks after the index ED visit, categorized as early return to school or late return to school (3 or more school days missed) [53]. 

Mental Health Utilization Questionnaire: We will assess the patient’s mental and behavioral health treatment based on previously developed methodology, assessing parent-reported treatment and services used and unmet needs [24, 25]. This questionnaire is available in English and Spanish and takes less than two minutes to complete.

### Outcomes

Our primary outcome is the presence of mental health sequelae, defined as a composite measure of clinically significant new or worsening in anxiety or depression 1 to 3 months following mTBI. This will be assessed using the GAD-7 and the PHQ-8. For the GAD-7, a clinically meaningful increase is defined as a rise of 4 or more points from baseline (pre-injury retrospective report) at either the 1- or 3-month follow-up. For the PHQ-8 a clinically meaningful increase is defined as a rise of 5 or more points from baseline at either the 1- or 3-month follow-up [44]. Thus, the primary outcome is binary and is considered met if a participant demonstrates a clinically significant increase on either the GAD-7 or PHQ-8 at 1 or 3 months post-injury.

We will assess secondary outcomes using data collected at the 1- and 3-month follow-up timepoints to further characterize the study cohort. While the primary outcome focuses on mental health sequelae, mTBI may impact other domains of functioning. These secondary outcomes will help provide a more comprehensive understanding of the broader consequences of mTBI and the context of mental health changes. We will evaluate the association between each secondary outcome and the predicted risk of the primary outcome based on our risk-stratification model. Additionally, we will explore potential risk factors for each secondary outcome, which include:

Decline in quality of life: Evaluated as a binary variable, a decline will be considered present if there is a decrease of 4.5 points or more in the PedsQL score at either the 1- or 3-month follow-up compared to baseline.

Persistent mTBI symptoms: Evaluated as a binary variable, persistent symptoms will be scored using the Rivermead. This outcome will be met if the participant reports a score of 2 or higher on any three symptoms at either follow-up point.

New emotional/behavioral difficulties or hyperactivity/inattention: These will be assessed using the SDQ. New emotional/behavioral problems will be defined as a 5-point or greater increase on the emotional symptoms subscale. New hyperactivity/inattention problems will be defined as a 6-point or greater increase on the corresponding subscale, compared to baseline scores, at either the 1- or 3-month follow-up.

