To complement the low-risk component of the risk stratification model created by recursive partitioning, we will use the same candidate variables to conduct multivariable logistic regression analyses to derive a risk score model for those patients identified as having greater than low risk (i.e. those who do not meet low-risk criteria). We will first conduct single variable logistic regression to identify all variables that have any association with the outcome.

Internal cross-validation methods will be used to refine the model. Following the development of the final model from the derivation cohort, we will use the Framingham Study method to translate logistic regression estimates into simple risk scores. Performance of the resulting risk-stratification models (original and simplified) will be validated in the validation cohort [55]. Model performance will include assessments of discrimination and calibration. Finally, we will also use random forests to derive a prediction algorithm for mental health sequelae. Many trees are independently grown using recursive partitioning on bootstrapped samples of observations. The predictor at each node in each tree is selected from a random subset of predictors and trees are grown without pruning.

Secondary outcomes will be analyzed using descriptive statistics to further characterize the study population. We will analyze how the primary risk model prediction is associated with secondary outcomes. For this analysis, we will use the combined derivation and validation cohorts.

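### The PedsQL secondary outcome is reduced to a yes/no fall of 4.5 points at either visit, with no continuous analysis named; this costs power for small effects, rare factors or a single cohort.

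*Protocol article*

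**What the plan says.** Validated questionnaires describes the instrument: "The PedsQL is measured as a continuous score that ranges from 0 to 100". It also gives the basis for the threshold: "a clinically meaningful difference is indicated by a 4.5-point change on the PedsQL scale". Table 1 schedules the PedsQL at baseline, 1 month and 3 months.

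Outcomes then fixes the secondary outcome: "Evaluated as a binary variable, a decline will be considered present if there is a decrease of 4.5 points or more". The fall counts whether it is seen at 1 month or at 3 months. A child therefore has two chances to cross the cut against one shared baseline.

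The article gives the secondary outcomes two uses beyond description. Outcomes says "we will explore potential risk factors for each secondary outcome". Analysis says "We will analyze how the primary risk model prediction is associated with secondary outcomes", using the combined derivation and validation cohorts. Analysis otherwise states: "Secondary outcomes will be analyzed using descriptive statistics to further characterize the study population". No analysis of the PedsQL as a score is named.

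**The concern.** A threshold for clinical importance is a good reason to report how many children cross it. It is not in itself a reason to replace the score with the flag when looking for associations. The primary outcome has to be binary because the tool classifies patients. The PedsQL has no such role here.

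Two things are at stake. First, factors with modest effects on quality of life are more likely to be missed with the flag than with the score already collected. Second, the reported proportion with decline will include some children who have not changed, because ordinary measurement error can produce a 4.5-point fall and the rule allows two attempts.

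**Working it through.** **The plan's own figures.** Sample size covers the primary outcome only.
- Derivation events: 1,400 × 0.25 = 350, as stated.
- Validation events: 1,080 × 0.25 = 270. At 90% sensitivity the 95% half-width is 1.96 × √(0.9 × 0.1 / 270) = 3.58% (Wald), or 3.76% by the exact or continuity-corrected method, which rounds to the stated 3.8%.
- Combined cohort for the predicted-risk association: 1,400 + 1,080 = 2,480.

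The article gives no SD, reliability, expected rate or power for the PedsQL. Those inputs are assumptions below.

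**Information kept by one cut.** For a normal variable cut so that a proportion p is positive, the relative efficiency is φ(z_p)² / [p(1 − p)].
- p = 0.5: 64%
- p = 0.3: 58%
- p = 0.2: 49%

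The loss is therefore at least 36%, whatever the SD.

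**Closed-form power, one visit.** Assume an SD of change of 12, N = 2,480, a factor in 10% (248 exposed, 2,232 not) and a 2-point effect.
- Continuous: SE = 12 × √(1/2,232 + 1/248) = 0.803; 2 / 0.803 = 2.49; power = Φ(2.49 − 1.96) = 0.70.
- Binary: flagged proportions are Φ(−4.5/12) = 0.354 and Φ(−2.5/12) = 0.417; the two-proportion test has power 0.51.
- At 3 points: 0.96 against 0.84. At 4.5 points: 1.00 against 0.99.

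**Simulated power, either-visit flag.** Logistic regression of the flag on factor and baseline, against linear regression of the mean follow-up score on factor and baseline; two-sided 5%. Assumed score SD 13 and correlation 0.7 between any two visits. Ranges cover separate simulation runs.

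| N | Factor present in | Effect (points) | Binary | Continuous |
|---|---|---|---|---|
| 2,480 | 10% | 1.5 | about 50-55% | 82-87% |
| 2,480 | 10% | 2 | 78-79% | 95-96% |
| 2,480 | 10% | 3 | about 98-99% | 100% |
| 2,480 | 10% | 4.5 | 100% | 100% |
| 2,480 | 5% | 3 | about 80-85% | 98-100% |
| 1,400 | 10% | 3 | about 89% | 99% |

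A final check of 1,000 simulated trials per row agreed with the two top rows to within about two percentage points.

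**Children with no true change who are flagged.** With measurement error SD (SEM) per score, the change has SD = SEM × √2, and the two changes correlate 0.5 because they share a baseline. One visit: Φ(−4.5 / (SEM × √2)). Either visit: twice that, less the bivariate normal probability that both cross.

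| Assumed SEM | One visit | Either visit |
|---|---|---|
| 2 | 6% | 10% |
| 3 | 14% | 23% |
| 4 | 21% | 33% |
| 5 | 26% | 40% |
| 6 | 30% | 44% |

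**The case against.** The strongest reply is that the cut is not arbitrary. The article ties 4.5 points to clinical importance, and the rule follows the form of the primary outcome, a meaningful change at 1 or 3 months. The outcome is secondary, meant to characterize the cohort, its risk-factor work is exploratory, and no power is claimed for it. The full analysis plan is not shown and may contain a continuous analysis. All of this stands. It makes the point one of efficiency and limits its priority, but it does not supply a reason to use only the flag for associations.

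Several stronger readings are tempting and are not supported:
- *That the flag loses much of the power for risk factors in general.* With 2,480 patients and a factor in 10%, the loss is negligible at the article's own 4.5 points and slight at 3 under the simulated assumptions.
- *That about half of stable children will be called declining.* The 48% obtained at SD 13 and correlation 0.7 treats all imperfect correlation as error (SD 13 × √0.3 ≈ 7.1). At an error SD of 2 points the share is about 10%. The article gives no value.
- *That the ±3.8% implies roughly 11% further loss to follow-up.* The exact interval with 270 events already gives it, and the article says that 1,080 accounts for loss.
- *That power should be judged in the validation cohort alone.* The predicted-risk association is assigned to the combined cohorts; the sample for the risk-factor work is not stated.
- *That the Rivermead outcome has the same fault.* Its rule is "This outcome will be met if the participant reports a score of 2 or higher on any three symptoms at either follow-up point". A rating of 2 is the first level worse than before injury, so the item cut has a visible basis, and a total score would also count symptoms that have not worsened.

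**Conclusion.** The point holds as an avoidable inefficiency, not as a contradiction or an error in the article's figures. The information loss of at least 36% needs only normality. The power loss is material for effects of about 1.5 to 2 points, and at 3 points when the factor is rare (5%) or only the derivation cohort is used. Those figures rest on the assumed SD 13 and correlation 0.7. The share of unchanged children flagged is 10% to 44% for an error SD of 2 to 6 points, against 6% to 30% at a single visit, and it depends wholly on that assumed error. Priority is low to moderate.

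**What to change.** For the predicted-risk and risk-factor analyses of the PedsQL, prespecify a linear repeated-measures model of the 1- and 3-month scores, adjusted for the baseline score. Keep the 4.5-point fall as a clinically interpretable descriptive proportion, and report it at each visit as well as for either visit.

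The cost is analysis wording and a few more models: no new data, visits or patients. The downside is two forms of one outcome to report, so the text should say which one answers the association questions. Study status describes enrollment as ongoing, with analyses to begin after follow-up ends, so this can still be prespecified. If the full analysis plan already contains such a model, a sentence in the article saying so would be enough.

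### The SDQ secondary outcome turns absolute cutoff scores (5 and 6) into required point increases, so it does not identify new problems as the protocol itself defines them

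*Protocol article*

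**What the plan says.** The SDQ paragraph under Validated questionnaires treats 5 and 6 as scores that classify a child's status: "We will use a cutoff score of 5 or more points to define psychological distress and 6 or more points to define hyperactivity/inattention". It adds that fewer than 10% of the population score that high. Each of the two subscales has five items with three response levels.

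The Outcomes section then defines the secondary outcome with the same two numbers as changes. For the first subscale: "New emotional/behavioral problems will be defined as a 5-point or greater increase on the emotional symptoms subscale". For the second: "New hyperactivity/inattention problems will be defined as a 6-point or greater increase on the corresponding subscale". Both rises are measured from baseline and may occur at 1 month or at 3 months. The cutoffs are not applied as cutoffs anywhere after they are introduced.

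The other outcomes that compare with baseline are handled differently. The GAD-7, PHQ-8 and PedsQL each have a minimal important or clinically meaningful difference with a citation (4, 5 and 4.5 points), and the Outcomes section uses those figures for change. The SDQ has none.

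**The concern.** A cutoff score says where a child stands. A change threshold says how far the child has moved. A number chosen for the first purpose has no standing for the second without separate support, and none is given. As written, the outcome is labelled new but measures neither a new crossing of the stated cutoff nor a change known to be important.

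The outcome is used. The Abstract lists new behavioral or emotional difficulties among the secondary outcomes. The Outcomes section plans to explore risk factors for each secondary outcome. The Analysis section plans to relate the primary model's predicted risk to the secondary outcomes in the combined cohorts. If a child just below the cutoff needs a near-maximal follow-up score to qualify, those associations will partly reflect how the rule depends on baseline score.

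**Working it through.** **Inputs.** Cutoffs of 5 (emotional) and 6 (hyperactivity), five items per subscale and three response levels come from Validated questionnaires. Required rises of 5 and 6 come from Outcomes. The protocol gives no event rate or sample size for the SDQ outcome, so there is no stated figure to reproduce.

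**Assumption.** Item scores are not printed. I take 0/1/2, giving a range of 0 to 5 × 2 = 10. Scoring 1/2/3 would put every child at 5 or more, against the stated base rate under 10%. The span is 10 points either way.

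**Step 1: size of the required rise.** The SDQ rule needs 5/10 = 50% (emotional) or 6/10 = 60% (hyperactivity) of the full scale. The GAD-7 rule needs 4/21 = 19%, the PHQ-8 rule 5/24 = 21% and the PedsQL rule 4.5/100 = 4.5%.

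**Step 2: all score pairs that newly reach the cutoff c.** New means baseline < c and follow-up ≥ c. The written rule counts a pair if follow-up − baseline ≥ c.

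| Baseline | Emotional (c = 5): score needed | Counted | Missed | Hyperactivity (c = 6): score needed | Counted | Missed |
|---|---|---|---|---|---|---|
| 0 | 5 | 6 | 0 | 6 | 5 | 0 |
| 1 | 6 | 5 | 1 | 7 | 4 | 1 |
| 2 | 7 | 4 | 2 | 8 | 3 | 2 |
| 3 | 8 | 3 | 3 | 9 | 2 | 3 |
| 4 | 9 | 2 | 4 | 10 | 1 | 4 |
| 5 | already at cutoff | – | – | impossible | 0 | 5 |
| Total | | 20 of 30 | 10 of 30 | | 15 of 30 | 15 of 30 |

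So an emotional move from 4 to 8 crosses the cutoff and is not counted. One pair is wrongly included: emotional 5 to 10, where the child was at the cutoff from the start. Hyperactivity has no wrongly included pair, but a child at 5, below the cutoff, cannot qualify even at the maximum.

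**Step 3: weighting by plausible distributions (all assumed).** Pair counts ignore how common each pair is. I used beta-binomial scores with one follow-up, baseline means of 1.0–2.0 (emotional) or 2.0–3.0 (hyperactivity), dispersion 3, 5 or 8, a mean rise of 0–2 points and a latent correlation of 0.3–0.8. Only settings with a baseline rate at or above the cutoff under 10% were kept.

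| Subscale | Settings kept | Share of new crossings missed: range | Median | Settings in which more than half are missed |
|---|---|---|---|---|
| Emotional | 60 | 24%–99% | 65% | about 73% |
| Hyperactivity | 48 | 46%–99.9% | 85% | about 98% |

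**The case against.** **Most new problems are missed.** A reader might infer this, but the protocol gives no SDQ distribution, retest correlation or expected change. By pair count the loss is one third (emotional) and one half (hyperactivity). In Step 3 it falls as low as 24% for the emotional subscale. Many, plausibly most, is as far as the evidence goes.

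**Crossing a cutoff is not the same as truly getting worse.** This is fair. Consider a simulation with normal latent scores rounded to 0–10, assumed means of 2 and 3, 10–12% at or above the cutoff at baseline, retest correlation 0.6–0.8, 20% of children worse by 2–3 points and two follow-ups. In it, 32–52% of new crossings came from children who had not been made worse. Low capture rates measured against all crossings therefore make the rule look worse than it is. Among the truly worsened children, it still missed more than half in those runs, so the direction stands.

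**Many children can never meet the outcome.** The rule is unreachable from emotional baselines of 6–10 and hyperactivity baselines of 5–10. All of these except hyperactivity 5 are already at or above the cutoff and could not be new cases under any sensible definition. Only hyperactivity 5 is wrongly shut out.

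**The outcome will be nearly empty or uninterpretable.** The documents do not support this. In the same simulation the rule flags 0.7–5.9% (emotional) and 0.1–2.8% (hyperactivity). Over the planned 1,400 + 1,080 = 2,480 children that is about 17–146 and 2–69 events: sparse, and at the low end too few for hyperactivity, but not empty across the range. Its 10–12% starting rate also sits above the protocol's base rate of under 10%. A large rise can still be interpreted as a large rise; the label new is what fails.

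**A change-based outcome may be intended.** That would match the other instruments, but then a threshold justified for the SDQ is needed.

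**Conclusion.** The concern holds in this form: the two sections use the same numbers for different purposes and must be reconciled. The rule as written misses 10 of 30 (emotional) and 15 of 30 (hyperactivity) newly crossing score pairs, counts one pair that is not new, and blocks one baseline score that is below the cutoff. These counts rest only on the 0/1/2 item scoring. The proportion of children affected rests on distributions that the protocol does not state.

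The effect is confined to one secondary outcome. The GAD-7/PHQ-8 primary outcome, the derivation and validation of the prediction tool, and the sample size are untouched. It should be fixed, but it does not threaten the main result. Nor is it a detail left to an analysis plan, because the protocol fixes an explicit numerical rule.

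**What to change.** Before analysis, replace the two sentences in Outcomes with a definition that uses the protocol's own cutoffs:

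- New emotional difficulty: emotional score below 5 at baseline and 5 or more at 1 or 3 months.
- New hyperactivity/inattention: score below 6 at baseline and 6 or more at 1 or 3 months.
- Denominator: children below the relevant cutoff at baseline.
- Report the continuous SDQ change for all children alongside.

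If a change-based outcome is intended instead, cite a justified SDQ change threshold and call the outcome worsening rather than new.

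The cost is two sentences, plus any registry text that repeats them (not seen here). No new data are needed: Table 1 schedules the SDQ at baseline, 1 month and 3 months. The narrative list of baseline measures omits the SDQ and can be aligned in the same edit. Study status says enrollment is ongoing and analyses start after follow-up ends, so the change can precede results. The drawback is that crossing a cutoff also counts small rises such as 4 to 5; the continuous report offsets this.
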